#### 2.7.2 Secondary outcomes

a) Pittsburgh Sleep Quality Index (PSQI). PSQI is suitable for evaluating the sleep quality of patients, has 7 main dimensions such as sleep quality, sleep duration, sleep disorders, etc., a total of 18 points self-assessment entries consisted of, and each dimension is scored on a 4-point scale from 0–3. The total PSQI score ranges from 0–21, with higher scores indicating poorer sleep quality. b) Self-rating anxiety Scale (SAS). The SAS is used to assess somatic symptoms associated with anxiety responding. The SAS has 20 items, each of which is rated on a 4-point scale of 1–4. Individual scores on the 20 items are summed, multiplied by 1.25 and rounded to the nearest whole number. A score below 50 is considered normal, 50–59 is considered mild anxiety, 60–69 is considered moderate anxiety, and a score of 70 or more is considered severe anxiety.

### 2.8 Safety assessment

During the trial period, we will systematically collect, assess, report, and manage adverse events (AEs) through both solicited and spontaneous reporting mechanisms. Solicited AEs will be actively monitored using a standardized questionnaire focusing on common acupuncture-associated adverse events (e.g., needling pain, local bleeding, hematoma, dizziness) at each treatment session. Spontaneously reported AEs will be continuously documented throughout the study period based on participants’ voluntary reports. All AEs will be assessed for severity (mild, moderate, or severe), duration, outcome, and their relationship to study intervention (unrelated, possibly related, or definitely related).

The trial clinicians will receive standardized training on AE recognition, assessment, and reporting procedures. Each AE report will be initially evaluated by the treating acupuncturist and subsequently reviewed by an independent safety monitoring committee. For severe AEs, the acupuncturist will provide immediate appropriate care and notify the principal investigator within 2 hours. All severe AEs will be reported to the ethics committee within 24 hours and followed up until resolution. Cumulative AE data will be reviewed monthly by the safety monitoring committee to identify any safety concerns requiring protocol modification. The frequency and severity of AEs will be summarized and reported in the final trial results according to CONSORT guidelines for harm reporting.

### 2.10 Statistical analyses

The data are analyzed using IBM SPSS (V.25.0), and all statistical tests are taken as two-sided tests. The statistical significance is set at P<0.05. In terms of descriptive statistics, continuous variables will be expressed as mean ± standard deviation, while categorical variables will be expressed as frequencies and percentages.

In terms of comparisons of measurements, as the HAMA, PSQI, and SAS scores are ordinal, non-parametric tests are prioritized for analyzing group differences. For between-group comparisons of HAMA, PSQI, and SAS scores, Mann-Whitney U test will be used; for within-group (pre- and post-test) comparisons, Wilcoxon signed-rank test will be applied. For categorical variables, Chi-square or Fisher’s exact tests will be used as appropriate.

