## Abstract

**Introduction:**

Generalized anxiety disorder (GAD) is the most common type of anxiety disorders. GAD usually occurs in adolescence or early adulthood, and the prevalence of GAD is higher among college-enrolled young adults than in the general adult population. However, there is a lack of evidence regarding the effectiveness of acupuncture in the treatment of GAD. This study’s objective is to evaluate the efficacy of acupuncture in the treatment of GAD in college students and its stability.

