## 2. Methods

### 2.1 Study design overview

This is a single-center, prospective, sham acupuncture controlled, randomized controlled trial. Patients will receive 2 courses of acupuncture + conventional medication or sham acupuncture + conventional medication after randomization. The schedule of enrollment, intervention, and assessment is shown in Fig 1. Each patient will be treated for 4 weeks, with a late follow-up of 2 months; this includes baseline assessment (week 0), end of treatment period II (week 4), end of 1 month of follow-up, and end of 2 months of follow-up (Fig 2). The reporting of this study protocol is based on the Consolidated Standards of Reporting Trials (CONSORT) checklist [12] and the Standards of Reporting Trials and Revised Standards for Reporting Interventions in Clinical Trials of Acupuncture (STRICTA) checklist [13].

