### 2.3 Sample size

Following Cohen’s statistical power analysis guidelines, [15] we determine that a medium effect size (d = 0.50) is appropriate for this study, given the absence of preliminary data or prior research that could offer specific effect size estimates. In situations lacking pilot data, selecting a medium effect size is recommended to balance statistical power requirements and resource constraints, while ensuring the ability to detect clinically meaningful differences. Since our primary outcome measure (HAMA score) is a continuous variable that will be compared between groups using means, we applied Cohen’s recommendations for t-tests between independent means. According to these guidelines, 64 subjects per group are required to detect a medium effect size (d = 0.50), with type-I error (α) = 0.05 and power (1-β) = 0.80. Accounting for an anticipated 10% dropout rate, we will recruit 71 subjects per group, resulting in a total sample size of 142 participants. This sample size calculation ensures adequate statistical power to detect clinically meaningful differences between groups while accounting for potential attrition.

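### The between-group test fixed in Section 2.10 leaves out the baseline scores, and no contrast over time is tied to the stability objective

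*Protocol article*

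**What the plan says.** Section 2.10 sets the between-group method for the primary and both secondary scales: "For between-group comparisons of HAMA, PSQI, and SAS scores, Mann-Whitney U test will be used". It adds that "for within-group (pre- and post-test) comparisons, Wilcoxon signed-rank test will be applied". Neither statement names a covariate, a visit or a comparison between visits. The reason given for rank methods is that the three scores are ordinal.

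Section 2.3 takes a different view of the same outcome. It treats HAMA as continuous, to be compared by means, and sizes the trial with a t-test: "64 subjects per group are required to detect a medium effect size (d = 0.50". That calculation is made "with type-I error (α) = 0.05 and power (1-β) = 0.80".

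Section 2.1 lists a baseline and three later assessments, the last two after treatment has ended: "this includes baseline assessment (week 0), end of treatment period II (week 4), end of 1 month of follow-up, and end of 2 months of" (the quote stops one word short of the end of the list). Section 2.7.1 makes HAMA at the three post-baseline visits the primary outcome and singles out none of them. According to the Abstract, the objective is to "evaluate the efficacy of acupuncture in the treatment of GAD in college students and its stability". Section 1 repeats the two aims, and stability is not defined in either place.

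**The concern.** The analysis does not fit the design in two respects.

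- **Baseline.** A Mann-Whitney test has no place for a covariate, so the comparison of the arms ignores a measurement that usually predicts the outcome. Section 2.5 describes permuted blocks with no stratification by severity, so baseline is not used in the allocation either. It is used only within each arm. There, a before-after p-value mixes any treatment effect with natural course, regression to the mean (entry depends on HAMA) and the conventional medication that Section 2.1 gives to both arms.
- **Stability.** This is a question about how the between-group effect behaves after treatment ends. No planned analysis estimates that. A significant result at week 4 and a non-significant one at month 2 would not show that the effect had faded, because the two results are never compared.

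At stake are precision in the main comparison and a matching analysis for one of the two stated aims.

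**Working it through.** **Inputs from the document.** d = 0.50, α = 0.05, power 0.80 and 64 per arm before dropout (Section 2.3); two-sided testing, Mann-Whitney between groups (Section 2.10); HAMA 7 to 21 at entry (Section 2.2). **Assumed:** the baseline-outcome correlation r, which the document does not give, and normally distributed scores.

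**1. The plan's own figure.** Solving the two-sample t-test (noncentral t) for d = 0.50 and 80% power gives 63.77 per arm, so 64. The stated figure reproduces. At 64 per arm the noncentrality is 0.50 × √(64/2) = 2.83 and power is 0.801.

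**2. The test actually planned.** With normal data, the efficiency of Mann-Whitney relative to the t-test is 3/π = 0.955. The effective sample is 64 × 0.955 = 61.1 per arm, and power is 0.783. Simulation (10,000 runs per setting) gave 0.778 to 0.787.

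**3. With baseline adjustment, one visit.** The residual SD shrinks by √(1 − r²), so the effective standardised effect is 0.50/√(1 − r²).

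| Analysis, 64 per arm | Effective d | Power |
|---|---|---|
| Mann-Whitney (planned) | – | 0.78 |
| Unadjusted t-test | 0.500 | 0.80 |
| ANCOVA, r = 0.2 | 0.50/0.980 = 0.510 | 0.82 |
| ANCOVA, r = 0.3 | 0.50/0.954 = 0.524 | 0.84 |
| ANCOVA, r = 0.5 | 0.50/0.866 = 0.577 | 0.90 |

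Simulated ANCOVA power was 0.836 at r = 0.3 and 0.898 at r = 0.5.

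**4. What the gain consists of.** At r = 0.2 the step from 0.78 to 0.82 is about half due to leaving the rank test (0.783 to 0.801) and half due to baseline (0.801 to 0.817). At r = 0.5 most of it is due to baseline (0.801 to 0.900). These figures are for an analysis of means. An adjusted rank or ordinal analysis would start from the 0.78 line, and its power was not computed.

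**5. Stability.** The objective concerns persistence, and the visits needed to study it are scheduled (Sections 2.1 and 2.7.1). Section 2.10 offers only a two-sample test and a within-arm test. Neither yields the difference between the week-4 effect and the month-2 effect. With equal SDs and correlation ρ between those two visits, the standard error of that difference is √(2/64) × √(2(1 − ρ)). At an assumed ρ = 0.5 it is 0.177 × 1 = 0.177 SD, giving a 95% half-width of 1.96 × 0.177 = 0.35 SD. The trial can estimate the change, though not tightly.

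**The case against.** The strongest defence is that a Mann-Whitney comparison of randomised arms is a valid test, chosen for a stated reason, and that the benefit of adjustment rests on an unknown correlation. Entry is limited to HAMA 7 to 21, and a restricted range tends to lower that correlation. At r = 0.2 the gain over the planned test is only about 4 percentage points. A mixed model also treats the score as interval and changes the estimand to a mean difference, which goes against the ordinal rationale in Section 2.10. All of this stands. It limits the size of the point and the choice of remedy, but it does not remove the point: adjustment gains power at any non-zero correlation, and adjusted methods exist that respect an ordinal scale.

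A reader might also infer stronger things that the document does not support:

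- *That the plan cannot address stability.* Mann-Whitney tests at months 1 and 2 would show whether a difference is present then. What is missing is a definition and a contrast over time. That a test is run at each visit is itself inferred from Section 2.7.1.
- *That baseline is not used at all.* The Wilcoxon tests use it as the pre-test value. Only the between-group comparison omits it.
- *That chance imbalance biases the result.* With 71 per arm, the baseline difference exceeds 1.96 × √(2/71) = 0.33 SD in 5% of trials. At r = 0.5 that moves the unadjusted comparison by 0.33 × 0.5 = 0.16 SD. The standard error already covers this. It is the same precision loss seen another way, not bias.
- *That participants who miss a visit are dropped.* Section 2.10 says nothing on missing data, which an article may leave to the full plan. Section 2.9 invites those who stop treatment to continue follow-up.
- *That one arm will often be significant and the other not, and be read as efficacy.* If both arms improve equally and each test has power p (paired t approximation, n = 64), the chance of a split is 2p(1 − p). It runs from about 0.22 at a change of 0.1 SD, through a peak of 0.50, to 0.05 at 0.5 SD and under 0.01 at 0.6 SD. The document gives no expected change and does not say that efficacy will be judged this way.

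**Conclusion.** The point holds as an improvement in efficiency and in the match between objective and analysis. It is not an error that invalidates the trial. Section 2.10 itself fixes the unadjusted test, so this is a stated choice and not a detail left to an unseen analysis plan. On normal data at d = 0.50 and 64 per arm, power moves from about 0.78 to between 0.82 and 0.90 for assumed correlations of 0.2 to 0.5, with the lower end quite possible given the entry range. Even at 0.2, adjustment brings power above the 0.80 that Section 2.3 claims and that the planned test slightly misses. The gap on stability does not depend on any assumed figure: the aim is stated, undefined and tied to no contrast.

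**What to change.** Revise Section 2.10 before unblinding.

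- **Settle the scale.** Reconcile the continuous view of HAMA in Section 2.3 with the ordinal view in Section 2.10, since this decides the model.
- **Adjust for baseline.** If HAMA is taken as continuous, use a repeated-measures mixed model with arm, visit, arm-by-visit and baseline score. If the ordinal rationale is kept, use a proportional-odds model or rank ANCOVA with baseline. Treat PSQI and SAS in the same way.
- **Name the contrasts.** Make the between-group contrast at week 4 primary. Assess stability by the between-group contrasts at months 1 and 2, together with the change in the between-group effect from week 4 to month 2. Report that change with its confidence interval, and do not read a non-significant change as proof of stability.
- **Within-arm results.** Report the changes descriptively and do not use them as evidence of efficacy.

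The cost is revised wording and slightly more analysis work. The mixed model also requires accepting the score as interval and a mean difference as the estimand.

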## 3. Discussions

Mental disorders in young people are a worldwide public health problem. Major depressive episodes and GAD are the most common mental disorders among college students [18]. College is the first step toward independent living, and it is a critical period for individuals to form their lifestyles and mental states as they grow up; during this period students must adequately manage their relationships with classmates and roommates outside of their busy academic schedules, and at the same time, Chinese college students face severe employment pressures [19]. Therefore, therapeutic interventions for anxiety sensitivity and psychological distress in GAD patients during this period to develop a healthy psychological state will have a positive impact on their later life [19,20].

There are evidences that acupuncture is effective in the treatment of GAD and relieve patients’ anxiety symptoms [21,22]. Due to the cultural background, it is difficult to blind patients in China. Therefore, we choose the Streitberger needles as the treatment for the control group. The Streitberger needles could simulate the acupuncture process without piercing the skin, [23] and studies have shown its credibility in the effectiveness of acupuncture [24]. Meanwhile, prone position will be used and non-meridian non-points on the back will be selected for further blinding in the control group.

The HAMA is one of the most used rating scales to measure the severity of anxiety symptoms, [25] which is still in use today, and the reliability and validity of the scale are adequate [26]. Therefore, HAMA is the primary outcome of this study. Secondary outcomes are PSQI and SAS. In addition to psychological disorders, patients with GAD exhibit a variety of physical symptoms, such as insomnia, which is characterized by difficulty falling and staying asleep or waking up early; insomnia is associated with the development and progression of GAD [27]. The PSQI is one of the most widely used sleep indicators, and sleep quality scores are correlated with academic performance, mental health, and substance use problems, thus further demonstrating the importance of a good night’s sleep for college students [28]. The SAS that developed in 1971 and still widely used in research, is commonly used to measure physical symptoms associated with anxiety reactions [29]. The SAS has good psychometric properties and is one of the scales used to successfully screen for anxiety disorders [30]. As a self-report questionnaire, the SAS is convenient in assessing anxiety [31].

Major limitations of this study are as follows. First, it is not possible to blind the acupuncturists, which could potentially introduce bias. Second, Streitberger needles are relatively less used in acupuncture clinical trials in China. Although this type of needle is an effective tool to blind participants who receive acupuncture due to its unique design, it may limit the generalizability of our findings to real-world acupuncture practice and research contexts in China.

## 4. Conclusions

In conclusion, this trial will provide a basis for the efficacy of acupuncture in the treatment of GAD in college students as a clinical practice, which will help acupuncturists to make the right decisions when treating GAD in college students.
